## Abstract

**Background:**

Impaired brain bioenergetics is a pathological hallmark of Alzheimer’s disease (AD) and is a compelling target for AD treatment. Patients with AD exhibit dysfunction in the brain creatine (Cr) system, which is integral in maintaining bioenergetic flux. Recent studies in AD mouse models suggest Cr supplementation improves brain mitochondrial function and may be protective of AD peptide pathology and cognition.

**Aims:**

The *Creatine to Augment Bioenergetics in Alzheimer’s disease (CABA)* study is designed to primarily assess the feasibility of supplementation with 20 g/day of creatine monohydrate (CrM) in patients with cognitive impairment due to AD. Secondary aims are designed to generate preliminary data investigating changes in brain Cr levels, cognition, peripheral and brain mitochondrial function, and muscle strength and size.

**Methods:**

CABA is an 8-week, single-arm pilot study that will recruit 20 patients with cognitive impairment due to AD. Participants attend five in-person study visits: two visits at baseline to conduct screening and baseline assessments, a 4-week visit, and two 8-week visits. Outcomes assessment includes recruitment, retention, and compliance, cognitive testing, magnetic resonance spectroscopy of brain metabolites, platelet and lymphocyte mitochondrial function, and muscle strength and morphology at baseline and 8 weeks.

**Discussion:**

CABA is the first study to investigate CrM as a potential treatment in patients with AD. The pilot data generated by this study are pertinent to inform the design of future large-scale efficacy trials.

**Trial registration:**

ClinicalTrials.gov, NCT05383833, registered on 20 May 2022.

## Introduction

Alzheimer’s disease (AD) affects more than 1 in 8 Americans over the age of 65 and is expected to grow in prevalence over the coming decades [1]. Historically, the pipeline of therapy development has been relatively futile, leaving few therapeutic options for patients with AD [2]. Much effort in advancing therapies in AD has been focused on halting deposition of and removing amyloid-beta (Aβ) plaque deposits in the brain, a pathological hallmark in the development of AD. Although recent trials suggest new treatments may be promising for removing Aβ from the brain [3, 4] and modestly improving cognitive symptoms in humans with AD [5], it is likely that additional therapies will also be required to treat and prevent symptomatic AD.

Interventions that target brain energy metabolism are also emerging as promising disease modifying therapy approaches for AD and for its prevention [6, 7]. Impaired brain bioenergetics precede symptomatic AD and are increasingly acknowledged as a contributor to its pathology [8]. Patients with AD exhibit dysfunction in the brain creatine (Cr) system [9], an integral system for maintaining brain energy flux. In the brain, free Cr is phosphorylated to form phosphocreatine (PCr), a primary means of storing and transporting high-energy phosphates derived from both cytosolic and mitochondrial metabolism [10]. In AD, the creatine kinase brain isoenzyme (BB-CK) responsible for phosphorylating Cr in the cytosol is severely reduced [11], as are both free Cr and PCr [12]. Impairments in the brain Cr system in AD may limit the ability to meet the high constant energy demand of the brain and potentially signal mitochondria to downregulate ATP production [13].

Creatine monohydrate (CrM) is an oral nutritional supplement that has been used extensively as an ergogenic aid for sport and exercise and has had growing interest in its possible brain health benefits [14]. It safely increases Cr levels in skeletal muscle [15], yet its effect on brain Cr levels has been inconsistent in the few small studies that have been completed with varying doses and durations [16–21]. In humans, limited but encouraging data suggest that CrM improves cognition in both younger and older adults [22], particularly in pathological brain conditions [23]. In animals, CrM supplementation has been shown to preserve bioenergetic function of hippocampal neurons and protect against brain aggregation of Aβ [24]. Recently, an 8-week CrM intervention in the 3xTg mouse model of AD improved hippocampal mitochondrial respiration in both male and female mice [25]. Female mice also improved cognition and decreased Aβ peptide aggregation in the hippocampus [25]. These data suggest that CrM improves the symptoms associated with AD in a mouse model.

Despite evidence in animal models that CrM may be neuroprotective, there have been no trials investigating CrM as a potential treatment in patients with AD. We are currently conducting a single-arm open-label pilot trial, *Creatine to Augment Bioenergetics in Alzheimer’s disease* (CABA), designed to investigate the feasibility of CrM supplementation and generate preliminary efficacy data pertaining to both function and mechanisms in the brain and periphery in patients with AD.

## Study aims and objectives

The primary aim of CABA is to investigate whether 8 weeks of 20 g/day of CrM supplementation is feasible in patients with dementia due to AD. Our secondary aims are to generate preliminary data investigating changes in (1) total creatine concentration in the brain, (2) cognition, (3) mitochondrial biomarkers in the periphery and brain, and (4) muscle function and morphology coincident with the 8-week CrM intervention.

## Design and method

The CABA protocol follows the guidelines for reporting non-randomized pilot and feasibility trials [26]. The study protocol has been approved by the Institutional Review Board at the University of Kansas Medical Center, and the trial has been registered with ClinicalTrials.gov (NCT05383833).

### Trial design

CABA is a single-arm, open-label, pre-post pilot trial. We will recruit 20 participants with AD, and all will be assigned to the 20 g/day CrM supplement intervention for 8 weeks. This dosage has been shown to be feasible and safe in healthy older adults, and limited data suggest that it may raise Cr levels in the brain [22].

### Trial setting

CABA is a single-center trial at the University of Kansas Medical Center (KUMC) in Kansas City, KS. All study visits occur in person at the Hoglund Biomedical Imaging Center and the Landon Center on Aging, on campus buildings adjacent to each other in close proximity.

### Sample size

The primary aim of CABA is to investigate the feasibility of the CrM intervention; thus, formal estimates of power are not required [27]. This is the first human trial to investigate CrM supplementation in patients with AD. The secondary aims of CABA are designed to generate means and confidence estimates that inform sample size requirements of subsequent studies. With a sample size of 20, we will be able to estimate an 80% compliance rate with a 95% confidence interval of 62.5–97.5% and establish effect estimates and confidence intervals that can be used to inform the design of future large clinical trials.

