### Feasibility

The feasibility of the intervention will be based on compliance and safety. We also track the number of participants who are pre-screened for preliminary eligibility, contacted for recruitment, consent to enroll in the study, and withdraw from the study before or after allocation (Fig. 1).

The primary compliance measure will be based on participant completion of the study along with daily reported CrM intake on provided supplement calendars. Our criterion for compliance feasibility is constituted as ≥ 80% compliance with daily supplement intake among ≥ 80% of the study sample (*n* ≥ 16). Participants also bring the remainder of unconsumed CrM to 4-week and 8-week visits to be weighed by the study team to aid in determining compliance.

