### Progression to a larger clinical trial

Meeting our primary feasibility goal of 80% compliance with the intervention protocol (*n* ≥ 16 participants that report consuming ≥ 80% of the CrM doses) will constitute a successful study, regarding feasibility. To support progression to a future randomized, controlled trial investigating differential effects of CrM and placebo on brain health outcomes in patients with AD will require both demonstration of feasibility and a positive signal from any of our secondary physiology or cognition outcomes. These measures were designed to generate preliminary data on symptoms and physiology that may be relevant to AD; thus, any changes associated with the CrM intervention would warrant broader, large-scale investigation.

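### The stated 95% CI of 62.5–97.5% for 80% compliance with 20 participants is a Wald interval that sits too high at both ends; an exact or Wilson interval should replace it (minor correction)

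*Protocol article*

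**What the plan says.** The Sample size section of the protocol article states that, because the primary aim is feasibility, "thus, formal estimates of power are not required". It then gives a single precision figure, for 20 participants: "we will be able to estimate an 80% compliance rate with a 95% confidence interval of 62.5–97.5" per cent. No interval method is named. The same sentence adds that the trial will yield effect estimates and confidence intervals for planning later trials.

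The Trial design section fixes the sample at 20 in a single arm. The Data analysis section names compliance as the primary outcome. The Feasibility section sets the criterion as "≥ 80% compliance with daily supplement intake among ≥ 80% of the study sample", that is, at least 16 participants. The section on progression to a larger trial repeats it: reaching at least 16 compliant participants "will constitute a successful study, regarding feasibility". Neither section uses a confidence limit.

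**The concern.** A symmetric interval around 80% with only 20 participants suggests the normal approximation. A binomial proportion that far from one half has a skewed sampling distribution, and 20 × 0.20 = 4 expected non-compliers is too few for the approximation to be trusted. An interval printed as 95% may then not have 95% coverage, and its limits may be displaced.

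The lower limit is what a reader of a feasibility study looks at first, because it shows how poor true compliance could be when the target has just been met. The example in the Sample size section, 80% of 20, is also exactly the threshold case of the feasibility criterion. A displaced lower limit therefore makes a bare pass look somewhat more reassuring than the data would allow.

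**Working it through.** **Inputs.** n = 20 (Trial design; Sample size). Assumed rate p = 0.80, so 16 of 20 (Sample size; the same count is the criterion in Feasibility). Two-sided 95%, z = 1.96.

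**Step 1: reproduce the stated figure.** Wald: p ± z·√(p(1−p)/n).
- Standard error = √(0.80 × 0.20 / 20) = √0.008 = 0.0894.
- Half-width = 1.96 × 0.0894 = 0.1753.
- Interval = 0.6247 to 0.9753, which rounds to the stated 62.5–97.5%.

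Other candidates do not match: z = 2 gives 62.1–97.9%, a t quantile with 19 degrees of freedom gives 61.3–98.7%, n − 1 in the standard error gives 62.0–98.0%, and a continuity correction gives 60.0–100.0%.

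**Step 2: intervals suited to this sample size, for 16 of 20.**
- Clopper-Pearson: the lower limit is the 2.5% quantile of Beta(16, 5) and the upper limit is the 97.5% quantile of Beta(17, 4), giving 56.3% to 94.3%.
- Wilson: centre = (p + z²/2n)/(1 + z²/n) = (0.80 + 3.841/40)/(1 + 3.841/20) = 0.7517. Half-width = z·√(p(1−p)/n + z²/4n²)/(1 + z²/n) = 0.1677. Interval 58.4% to 91.9%.

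| Method | Lower | Upper | Width (points) | Stated lower minus this | Stated upper minus this |
|---|---|---|---|---|---|
| Wald (stated) | 62.5 | 97.5 | 35.1 | – | – |
| Wilson | 58.4 | 91.9 | 33.5 | 4.1 | 5.6 |
| Clopper-Pearson | 56.3 | 94.3 | 37.9 | 6.2 | 3.2 |

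Widths are from unrounded limits. The gap at the lower limit depends on the comparator: it is 3.3 points against Jeffreys (59.2–92.8%) and 6.8 against Wilson with continuity correction (55.7–93.4%).

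**Step 3: actual coverage at p = 0.80, n = 20.** Sum the binomial probabilities of the counts whose interval contains 0.80.
- The Wald interval contains 0.80 for counts 12 to 18. It lies wholly above 0.80 at 19 or 20 (probability 6.9%) and wholly below at 11 or fewer (1.0%). Coverage = 100 − 6.9 − 1.0 = 92.1%.
- By the same sum, Wilson covers 95.6% and Clopper-Pearson 97.8%.

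The Wald misses are lopsided: 6.9% of the time the interval is too high, against a nominal 2.5% per side.

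**Step 4: direct check of the stated limits.**
- At a true rate of 62.5%, the probability of 16 or more of 20 is 7.9%. An exact lower limit would make it 2.5%, which happens at 56.3%.
- At a true rate of 97.5%, the probability of 16 or fewer of 20 is 0.14%. It reaches 2.5% at 94.3%.

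So the lower limit excludes rates that remain compatible with 16 of 20, and the upper limit includes rates that are not.

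**The case against.** The strongest reply is that nothing has been miscalculated. The figure follows exactly from the article's own inputs, and coverage of 92.1% at the rate in question is imperfect rather than absurd. That stands: this is a poor choice of approximation, not a slip in arithmetic.

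Three stronger readings are tempting, and the article does not support them.

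- *That the sample size is undermined.* A reader might treat this interval as the sole basis for 20 participants. The section also relies on the feasibility aim needing no power calculation and on producing estimates for later trials, and it does not derive 20 from a target width. The width moves only from 35.1 to 33.5 (Wilson, narrower) or 37.9 points (exact).
- *That the feasibility or progression decision is affected.* A reader might infer this because the worked case is the threshold case. The rule is a count of at least 16, and no confidence limit enters it. No verdict would change.
- *That the results will be reported with impossible or degenerate intervals.* A reader might project the Wald method onto the analysis, where the untruncated upper limit passes 100% at 17 to 19 of 20, the interval has zero width at 20 of 20, and coverage falls to 81.9% at a true rate of 85% and 87.6% at 90%. The article names no interval method for the observed compliance proportion. The confidence intervals in Data analysis concern within-group change. These consequences are conditional on a choice that the article does not make.

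Nor is it a fault that the article does not fix a method for retention, consent or adverse-event proportions. A condensed article may leave that to the analysis plan. What remains is a figure that the article does print, for its primary outcome, and that is displaced at both ends.

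**Conclusion.** The point holds as a minor correction. The interval is presented as 95% but is a large-sample approximation used where it is unreliable. At a true rate of 80% it covers about 92%, and both limits are too high: the lower by 4.1 points against Wilson and 6.2 against Clopper-Pearson, the upper by 5.6 and 3.2. Just meeting the criterion at 16 of 20 leaves true compliance as low as about 56–58% compatible with the data, rather than 62.5%.

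This assumes that participants are independent, that each is classed as compliant or not, and that all 20 are in the denominator, as the criterion of 16 implies. The range of 4 to 6 points refers to the two methods recommended here.

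**What to change.** Replace the interval in the Sample size section with wording such as: *With n = 20, 16 compliant participants (80%) gives an exact (Clopper-Pearson) 95% CI of 56.3% to 94.3%.* If Wilson is preferred, the limits are 58.4% to 91.9%. Either is defensible; the method should be named, and the same one used when the observed compliance proportion is reported.

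The cost is one sentence and a stated lower limit about 4 to 6 points less favourable. Sample size, the count of at least 16, data collection and trial conduct do not change.

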### Participant eligibility criteria

The CABA trial aims to enroll an equal sample of males and females that have been diagnosed with cognitive impairment due to AD [28] with a mini-mental state exam (MMSE) score ≥ 17. Prior to enrollment, participants require stable dosage of AD-related medications (i.e., donepezil, memantine) for 30 days. Participants also require the cooperation of a study partner (spouse, relative, or close friend) to help facilitate the intervention and accompany the participant to all study visits. Table 1 summarizes the trial inclusion and exclusion criteria.

**Table 1 Tab1:** Participant eligibility criteria

**Inclusion criteria**
• Diagnosed cognitive impairment due to AD [28] • Agreed cooperation from a study partner • Speaks English as primary language • Age 60 to 90 • Stable AD medication for ≥ 30 days • BMI ≥ 18.5 kg/m^2^
**Exclusion criteria**
• Diabetes (types 1 or 2), cancer requiring chemotherapy or radiation within the past 5 years, or recent cardiac event (i.e., heart attack) • Other neurodegenerative disease • Ongoing renal disorder or abnormal renal or liver function • Use of medications or supplements that affect blood glucose (i.e., metformin) • Unable to undergo MRI • Clinical trial or investigational drug or therapy participation within 30 days of the screening visit • Non-English speakers • Inability to perform strength testing • Weight > 350 lbs • MMSE < 17

### Recruitment

Recruitment for CABA leverages the existing recruitment infrastructure at the KU Alzheimer’s Disease Research Center (KU ADRC) [29]. The KU ADRC Outreach, Recruitment, and Engagement (ORE) Core initially pre-screens potential participants from a database of individuals that have consented to be contacted by the KU ADRC about study opportunities. Potential participants that meet preliminary diagnostic criteria are then phone screened by the CABA study team to explain the study and attain brief medical history. Individuals that are interested in participating in CABA and meet initial eligibility requirements are invited to attend the formal screening/baseline visit to attain informed consent and confirm eligibility. The CABA recruitment flow is illustrated in Fig. 1.

**Fig. 1 Fig1:**
[figure not shown]
CABA recruitment and screening flow

### Intervention

Delivery of the intervention is facilitated by registered dietitians (RD). After all baseline assessments have been completed, RDs provide participants and their study partners with a 5-week supply of CrM powder (Life Extension, USA) along with written and verbal instruction on how to consume the CrM. Participants are instructed to stir 10 g (1 scoop) of CrM powder into liquid to consume in the midmorning and to repeat the same process in the evening for a total of 20 g each day. All participants receive another 5-week supply of CrM at the 4-week study visit, which provides enough CrM to each participant to complete the study. The additional week supply of CrM is intended to cover any error in study visit scheduling by 1 week (i.e., the 4-week visit at week 5 of intervention). Study partners are asked to assist participants in completion of a daily supplement calendar designed to track consumption of the two daily doses of CrM for the duration of the study. To encourage compliance and monitor for adverse events (AEs), the study RDs speak with participants and their study partners each week during planned telephone calls.

### Study visits and assessment timeline

Study flow and a description of the study visits and procedures are presented in Table 2. All study procedures take place over five visits: one screening/baseline visit, a second baseline visit within 1 to 2 weeks of the first visit, a 4-week visit, and two 8-week visits that occur within 1 week of each other.

**Table 2 Tab2:**
[figure not shown]
Study visit procedure summary

## Assessments

All study assessments and their associated objectives are presented in Table 3.

**Table 3 Tab3:** Study objectives and outcomes

Objective	Measurement	Timepoint
Aim 1: Feasibility	Recruitment and retention	Throughout study
	Self-reported compliance on Cr supplement calendar	Throughout intervention
	Serum creatine (Cr) levels	Baseline, 4 weeks, and 8 weeks
Aim 2: Brain creatine concentration	Magnetic resonance spectroscopy measurement of brain total creatine (Cr)	Baseline and 8 weeks
Aim 3: Cognition	NIH-Toolbox® Cognitive Battery	Baseline and 8 weeks
Aim 4: Peripheral mitochondrial function	OROBOROS Oxygraph-2 K measurement of platelet and lymphocyte respiration, ATP production, and ROS production	Baseline and 8 weeks
Aim 4: Brain mitochondrial function	Magnetic resonance spectroscopy measurement of brain N-acetylaspartate (NAA) and glutathione (GSH)	Baseline and 8 weeks
Aim 5: Muscle strength and morphology	Handgrip strength, leg extensor strength, and quadriceps ultrasound	Baseline and 8 weeks

### Feasibility

The feasibility of the intervention will be based on compliance and safety. We also track the number of participants who are pre-screened for preliminary eligibility, contacted for recruitment, consent to enroll in the study, and withdraw from the study before or after allocation (Fig. 1).

The primary compliance measure will be based on participant completion of the study along with daily reported CrM intake on provided supplement calendars. Our criterion for compliance feasibility is constituted as ≥ 80% compliance with daily supplement intake among ≥ 80% of the study sample (*n* ≥ 16). Participants also bring the remainder of unconsumed CrM to 4-week and 8-week visits to be weighed by the study team to aid in determining compliance.

### Safety

Safety is assessed by frequency and severity of reported AEs, proportion of participant withdrawals due to AEs, and monitoring of blood safety labs. Study personnel ascertain AEs and side effects during weekly telephone calls and at the 4-week and 8-week study visits. Participants also have continuous access to study personnel, which allows them to report potential AEs on a continuous basis. All AEs are immediately reported to the PI; assessed for severity, cause, and expectedness; and followed until resolution. Additional safety checks include monitoring change in lab values from a comprehensive metabolic panel and liver and renal function tests (Quest Diagnostics, USA).

### Cognitive testing

The mini-mental state exam (MMSE), a brief, multidomain cognitive test and dementia screening tool, is administered by trained study personnel at baseline as part of the screening procedures and again at 8 weeks.

Comprehensive cognitive testing is also completed at baseline and 8 weeks using the NIH Toolbox® (NIH-TB) cognitive battery [30]. NIH-TB has been validated in both cognitively normal and demented older adults [31]. The cognitive battery is facilitated by trained staff on an iPad (Apple, USA) and contains individual tests from cognitive domains of attention, category switching, episodic memory, working memory, speed of processing, written language, and auditory language. Unadjusted, age‐adjusted, and fully adjusted (age, sex, education) scores are automatically calculated for each individual test as well as a composite cognition score.

### Magnetic resonance imaging

High-resolution T1-weighted MRI is acquired using three-dimensional (3D) magnetization prepared rapid acquisition with gradient echo (MPRAGE) sequence (sagittal, 1 mm isotropic resolution, *TE/TI/TR* = 3.98/830/2000 ms, *FOV* = 256 × 256 mm^2^, 176 slices). The purpose of our T1-weighted MRI is to co-register magnetic resonance spectroscopy (MRS) scans and correct partial volume effects in MRS quantification.

### Magnetic resonance spectroscopy

Brain total Cr (tCr), N-acetylaspartate (NAA), and glutathione (GSH) concentrations are measured via MRS at baseline and 8 weeks on a 3 T MR system (Skyra, Siemens, Erlangen, Germany) using a 20-channel receiver RF coil, selecting an axial slab of the frontal and parietal regions above the lateral ventricle. Measuring brain tCr will provide insight into the effectiveness of our CrM intervention to increase brain Cr concentration. GSH is an important antioxidant defense system that reflects oxidative stress status [32] and, together with NAA, will provide insight into brain mitochondrial integrity [33, 34]. Our semi-LASER MRSI sequence for Cr and NAA (*TE/TR* = 38/2000 ms, *FOV* = 20 cm, matrix = 14 × 14, slice thickness = 25 mm, *VOI* = 80 × 80 mm^2^) and doubly selective multiple quantum-filtered MRSI sequence for GSH (TE/TR = 115/1750 ms, *FOV* = 200 mm, matrix = 10 × 10, slice thickness = 25 mm) [35, 36] minimize the effect of MR system instability and subject motion during the scan [37]. Metabolite signals from the frontal, parietal, and frontoparietal regions are quantified with LCModel software using water signals from the same slab of the brain as an internal frequency and concentration reference [38]. Metabolite concentrations in the gray and white matter are also calculated using an established regression method [39].

